### Data management

A psychologist from the research team will manage and monitor the data. All study information will be kept in secure drawers with limited access. Electronic data files will be password protected. Participant codes and personal information will be stored in a separate password-protected file. The data will be stored for 5 years after the end of the study, and only the study investigators led by the principal investigator will have access to the final data set. Results of the study will be presented through peer-reviewed publications and conferences. In addition, participants who request it will receive a report with the final results.

### Interventions

Four different meditative interventions will be assessed: (a) mindful breathing, which will be considered the control condition; (b) prostrations, according to Tibetan Buddhist tradition, (c) The Koan Mu, according to Zen Buddhist tradition, and (d) the mirror exercise, according to Toltec tradition. All participants in the four arms will receive these general instructions:- Formal practice should take 30–60 min/day. It can be divided into as many as 4 sessions/day at times of participants’ choosing, but the recommended times are after waking up in the morning and before going to bed at night.- There is no limit to the number of times informal practice can be performed during the day.- Use of a diary is necessary to record the time and duration of all formal and informal practices.- The intervention will have a duration of 60 days. During this period, participants are to take part only in the intervention to which they have been randomized and no other. After this period of time and during the follow-up, participants will be able to practise any kind of meditation and at times of their choosing, but this information must always be recorded in their diary.

Specific instructions for every intervention:Mindful breathing (I): paying attention to your breathing

Step 1. Assume a comfortable sitting posture, allowing the body slowly settle into position. You can take one or two deep breaths to draw your attention to your body. Then very gradually begin to notice your bodily sensations at that time (for example, your body making contact with the floor, mat or chair; the temperature of your skin; general sensations), until you come to include all the sensations of your entire body in general.Step 2. Very slowly start to become aware of your breathing. You can focus your attention on the movements of your chest or abdomen as you breathe in and out, or on the sensations of the air entering and exiting your nostrils as you breathe. It is important to follow the natural flow of your breathing, without trying to change it, simply observing and being aware of it, accepting what is happening in the present.Step 3. Your mind will eventually begin to wander. It is quite normal for your attention to be repeatedly distracted from your breathing and bodily sensations. This is not a problem. When you become aware of a certain distraction arising in your mind—whether in the form of a sensation, thought, feeling or sudden impulse—simply be aware that the mind is wandering, and allow the distractions to pass kindly, without becoming upset with yourself or judging them, and then redirect your attention to your breathing and your whole body.Step 4. You may experience intense sensations, such as pain in a part of your body, and you will find that your attention is repeatedly drawn away by such sensations from your chosen anchor (breathing or body). You may want to take advantage of this moment to deliberately decide to change your posture or to keep it and change the focus of your attention to those more intense sensations. If you choose this option, you can explore the sensations in more detail: How do you feel those sensations? Where? Do they change intensity or location over time? The aim is not to think about these things but what you feel. You can use your breathing to direct your attention to the area, by “breathing it”, as you would when practising body scan meditation.Step 5. Whenever your attention is drawn away by the intensity of the physical sensations or when your attention is distracted, you can reconnect with the present by directing your awareness to the movement of your breathing or the sensations of your whole body. Your awareness can then be expanded to take in all the sensations coming from all parts of your body.Step 6. Before the session ends, turn your attention back to the sensations of abdominal breathing. You can feel the connection with your inhaling and exhaling, instant by instant, perceiving your how you are anchored by your breathing and the feeling of balance. Slowly, when you feel ready, you can bring the practice to an end.

Mindful breathing (II): paying attention to your body

(Between steps 5 and 6)

After 10–15 min of mindful breathing, as previously described, allow your awareness to expand to all the sensations of your whole body. Gradually change the focus of your attention by moving away from your breathing and becoming aware of the sensation of your whole body and of how your sensations are continuously changing. You could feel your breathing throughout your body, as if it were breathing.

Besides your whole body and the sensations of breathing, you can include the sensations of the parts of your body in contact with the floor, chair, clothes or any other object.

If your mind wanders, which is its usual behaviour, be happy that you have become aware of this, observe where your mind has gone, and draw it back kindly to the sensation of your whole body.

If you experience unpleasant or painful sensations, follow the instructions previously given in steps 4 and 5.

When you are ready, you can bring the session to a close as described in step 6.

Mindful breathing (iii): paying attention to sounds, thoughts and emotions

(Between steps 5 and 6)• Sounds. Turn your attention to sounds. Get a feeling for where they come from, what their characteristics are, how they appear and disappear, where in the space around you the come from (above, below, besides, in front or behind you).

You need not follow the sounds; they happen without you having to seek them out. Do not think about them or label them; only experience them as simple auditory sensations (i.e. pay attention to their tone, pitch, volume and duration). Even if you hear words in your own language, do not think about their meaning; listen to them as if they were in a different language. Be aware of the more and less intense sounds, and of the space between sounds and of silence.

If your attention wanders, acknowledge kindly where it has gone and bring it back to the sounds. This will happen repeatedly.

Attention to sounds is a very powerful practice for expanding your awareness. You can continue with mindful breathing and move on to mindfulness of thoughts and sensations, or this can be a separate practice on its own.• Thoughts and emotions. Just as you have focused your attention on sounds, which are phenomena beyond your control and appearing in your mind autonomously, the thoughts that occur during meditation (unlike when you think voluntarily) are also beyond your control; they simply appear. Observe the process of how they appear, how they remain in your mental space, and how they disappear in a few seconds, without you having to do anything. You can even perceive the side of your mind in which they appear: from above, below, on the right or on the left. Do not try to stop them from appearing, speed up the process or wish them to disappear. Let them follow their natural process, as you did with the sounds.

Some people find it useful to imagine their mental space as a cinema screen and observe how thoughts appear on it, using the same process previously described. Another popular metaphor is to imagine your mind as the endless blue sky and thoughts as clouds that appear in it.

Attention without an object. To finish it, you might want to let go of the object on which you were focusing your attention (breathing, sounds, thoughts) and allow your field of awareness expand to include everything that appears in your mind and body. Simply try to relax your awareness, without anchoring it. Do not latch on to anything or want anything; simply observe what is happening with equanimity. When you are ready, you can bring the session to a close (as described in step 6).

As an informal practice, focus your attention on your breathing whenever you can during the day.(2)Postrations

The term “prostration” is generally used to describe an act of homage and respect. In Tibetan Buddhism, which is the most widespread form of *Vajrayana* Buddhism, the tantric path begins with special, or extraordinary, preliminary actions. These special preliminary actions are divided into five parts. The first of these is the Refuge practice, which is typically accompanied by prostrations. As explained by Kalu Rinpoche in his book *Foundations of Tibetan Buddhism*, prostrations are the physical element of the physical, verbal and mental aspects involved in the Refuge [25]. This practice includes a visualization (mental activity), a recital (speech activity) and a gesture/movement (bodily activity).

According to Patrul Rinpoche, as explained in his best-known book *Words of My Perfect Teacher*, prostrations are the antidote to pride, and it is important to combine the body, words and mind when performing them [26]. Therefore, the goals of this practice are to dissolve pride, purify the physical, verbal and mental dimensions, and unify and integrate these three spheres of the person.

Performing prostrations:

The practice begins with visualization. In this context, we have reduced it to the essentials in order to facilitate the practice. Visualize Shakyamuni Buddha in front of you, feeling that he is truly present. Visualize all beings beside you, feeling that they are not essentially different from you and that they are prostrated together with you. You should visualize the images with the consistency of a rainbow or hologram, not as solid entities. This should not diminish the feeling of their presence.

In the physical aspect, you start by cupping your hands to form the shape of a closed lotus flower that is about to open, leaving an empty space between them. The palms should not be pressed together without leaving a space, nor should they only be joined at the fingertips.^2^ Place your cupped hands on your head first, then at your throat and, finally, at your heart to purify the corruptions of the body (e.g. the actions of killing, stealing or harmful sexual conduct), the words (e.g. lying, causing arguments, harmful words or deceitfulness) and the mind (e.g. envy or covetousness, wishing harm on others). Next, touch the floor with five points of the body: the forehead, both palms of the hands and both knees.^2^ Once you have finished stretching out your body fully on the floor, you can raise your cupped hands over your head. Afterwards, when you stand up again, you straighten your body completely, cupping your hands again. Continue to perform prostrations in this way.

With regard to the words, each lineage recites their own verses, which in this case have been adapted to a simplified formula: “All beings and I prostrate ourselves before Buddha, who has transcended suffering. May all beings be able to transcend suffering.” This is recited while performing each prostration.

As the practice progresses, you can visualize how rays of light emanate from Buddha to tough your forehead, throat and heart, purifying your body, words and mind.

Quality is more important than quantity, the main indicators of which are the level of integration between the physical, verbal and mental actions and the feeling of presence in the visualization.

As informal practice, you can repeat the verse in your mind and perform the visualization whenever you can.(3)Koan Mu

*Koan* is a Japanese word for dialogue or question. It can be considered the hallmark practice of the schools of Zen Buddhism, mainly of Rinzai Zen. In this meditation, the student observes or concentrates on a single word or phrase for days or weeks. There are several books with collections of koans in the Zen tradition, and a type of progression has been described and used by meditation masters. One of the most famous ones that has been used by hundreds of masters for centuries with beginners is “Mu” or “Does a dog have Buddha-nature?”.

The koan is explained to the students in this way (Japanese version):

The result of the practice tends to be that by the 15th day, you discover that you no longer believe the story of your life and that it does not even matter to you. By changing masks, you learn to laugh at your own life. It reaches the point where you have nothing more to say, and you stand in front of the mirror changing masks. Nothing in your life makes you feel bad. Dreams tend to change to greater lucidity.

As informal practice, you should observe yourself in front of a mirror whenever you can. Masks are not required for the informal practice.

### Measurements

Evaluations will be performed at screening, pre-intervention, post-intervention and 3 and 6-month follow-up. All variables and assessment periods of the study can be found in Table 1.

**Table 1 Tab1:** Study outcomes

Instrument	Assessment area	Time to assessment
Sociodemographic	Gender, age, marital status, education, occupation, economic level	Screening
NETI	Deconstruction of self	Baseline, post-treatment and follow-up sessions
NADA	Nondual Awareness	Baseline, post-treatment and follow-up sessions
FFMQ	Facets and factors of mindfulness	Baseline, post-treatment and follow-up sessions
PHI	Well-being	Baseline, post-treatment and follow-up sessions
SOCS-O and SOCS-S	Compassion	Baseline, post-treatment and follow-up sessions
PANAS	Positive and negative affect	Baseline, post-treatment and follow-up sessions
OAV	Altered states of consciousness	Baseline, post-treatment and follow-up sessions

*NETI* Nondual Embodiment Thematic Inventory, *NADA* The Nondual Awareness Dimensional Assessment, *FFMQ* Five Facet Mindfulness Questionnaire, *PHI* Pemberton Happiness Index, *SOCS-0 and SOCS-S* Sussex-Oxford Compassion Scales, *PANAS* Positive and Negative Affect Schedule, *OAV* Altered State of Consciousness Rating Scale

#### Sociodemographic data and meditation experience

Participants will be asked about their gender, age (in years), nationality, current city of residence, marital status (single, married, cohabiting couple, separated/divorced, widowed or other), education (undergraduate/bachelor’s degree/diploma, master’s degree, doctorate and others) and for information regarding their experience with meditation, such as whether they have had meditation experience in general (“yes” or “no”), the mean in minutes for each time that they practised formal meditation, length of meditation experience (i.e. less than 1 year, between 1 and 3 years, between 4 and 6 years, between 7 and 9 years, or more than 10 years), the time (in months) that they may have interrupted their formal practice during their lives, and the percentage of their time dedicated to each type of formal meditation (concentrative or focused attention, open monitoring, compassion/loving-kindness, values, deconstructive/non-duality and informal practice). A brief explanation of each type of meditation practice will be provided. In addition, an open field is included so that participants can indicate other meditative techniques that they practice and have not been explicitly collected. The meditation information provided and collected will be based on author recommendations and previous studies [11, 27].

#### Main outcome

The Nondual Embodiment Thematic Inventory (NETI will be the primary outcome at post-intervention). This is a 20-item questionnaire designed to evaluate qualities of non-dual experience and spiritual awakening. The NETI assesses a number of facets, including frequency of non-dual experiences, which refer to self-transcendent states that have also been referred to as peak experiences (e.g. “Understanding that there is ultimately no separation between what I call my “self” and the whole of existence”) [28]. The items are rated on a 5-point scale with a score of 1 indicating “never” and 5 indicating “All of the time”. A total score, ranging from 20 to 100, is calculated by totalling the scores from all the items, with higher scores indicating higher levels of non-dual awareness. The scale has shown good psychometric properties in its original validation, with an internal consistency of Cronbach’s alpha = 0.91 [28, 29].

#### Secondary outcomes

##### The Nondual Awareness Dimensional Assessment (NADA)

This scale was developed to measure experiential effects of nondual awareness, such as bliss and self-transcendence. To study the trait, there is the NADA-T version with 13 items (e.g. “I have experienced all notion of self and identity dissolve away”), which are rated on a 5-point Likert-type scale ranging from “never or very rarely” to “very often or always”. On the other hand, to assess the state, the NADA-S version composed of 3 items and scored on a 10-point Likert scale (1 = Not at all, 10 = Very Much) will be used. Their psychometric properties are adequate (NADA-T: Cronbach’s alpha > 0.9; NADA-S: Cronbach’s alpha between 0.67 and 0.88) [30].

##### The Five Facet Mindfulness Questionnaire (FFMQ)

With 39 items (range 39–195 points) and five subscales: observing (e.g. “I am aware of the bodily sensations when O take a bath”), describing (e.g. “I find it hard to express what I feel”), acting with awareness (e.g. “I am easily distracted”), non-judging of inner experience (e.g. “I am aware that some of my thoughts are not normal, and I know that I shouldn’t feel that way”) and non-reactivity to inner experience (e.g. I think before reacting under stressful situations”). The items are rated on a Likert-type scale ranging between 1 and 5 points (from 1 = “never or very rarely true” to 5 = very often or always true”), and higher total values indicate better full mindfulness. The validated Spanish version of the questionnaire that has demonstrated appropriated psychometric properties will be used (Cronbach’s alpha > 0.80) [31, 32].

##### Sussex-Oxford Compassion Scales (SOCS)

The Sussex-Oxford Compassion for Others Scale (SOCS-O) and Sussex-Oxford Compassion for the Self Scale (SOCS-S) are two 20-item self-report scales measuring compassion. These are based on the theoretically and empirically supported definition of compassion as comprising five dimensions: (a) recognizing suffering (e.g., “I recognize when other people are feeling distressed without them having to tell me”), (b) understanding the universality of suffering (e.g. “I understand that everyone experience suffering at some point in their lives”), (c) feeling for the person suffering (e.g. When someone is going through a difficult time, I feel kindly towards them”), (d) tolerating uncomfortable feelings (e.g. “When someone else is upset, I try to stay open to their feelings rather than avoid them”) and (e) motivation to act/acting to alleviate suffering (e.g. When others are struggling, I try to do things that would be helpful”). The items are rated on a Likert-type scale ranging between 1 (“not at all true”) and 5 (“always true”) points. Their psychometric properties are adequate (SOCS-O: Cronbach’s alpha between 0.76 and 0.97; SOCS-S: Cronbach’s alpha between 0.74 and 0.97) [33].

##### The Pemberton Happiness Index (PHI)

The PHI is used to assess remembered well-being (general, hedonic, eudaimonic and social well-being) through 11 items rated on a Likert scale ranging from 0 (strongly disagree) to 10 (strongly agree). In addition, experienced well-being (positive and negative emotional events that may have happened the day before) is also measured through 10 items answered dichotomously (“yes” or “no”). The remembered well-being score is calculated with the mean score of the 11 items and varies from 0 to 10. The items for experienced well-being are transformed into a single score from 0 (zero positive experiences and 5 negative experiences) to 10 (5 positive experiences and no negative experiences). To calculate the overall PHI index, which included remembered and experienced well-being, individuals’ scores of the 11 items related to remembered well-being plus the sum of scores on the experienced well-being were summed; the total sum is then divided by 12, so the resulting PHI total mean score also ranges from 0 to 10. The Spanish validated version will be used in this study (Cronbach’s alpha > 0.80) [34].

##### Positive and Negative Affect Schedule (PANAS) [35]

This questionnaire comprises 20 items and two independent dimensions: positive affect (e.g. “interested”) and negative effect (e.g. “irritable”), with answers ranging in a Liker-type scale from 1 “very slightly or not at all” to 5 “extremely or very much”. Each scale has 10 items, and the score range for each is from 10 to 50. The Spanish version of the PANAS, adapted with adequate psychometrics and designed to assess affective states over the last week, will be used (Cronbach’s alpha between 0.87 and 0.91) [36].

##### Altered state of consciousness rating scale (OAV)

This is a 42-item scale grouped into 11 domains (i.e. experience of unity, spiritual experience, blissful state, insightfulness, disembodiment, impaired control and cognition, anxiety, complex imagery, elementary imagery, audio-visual synaesthesia and changed meaning of perceptions). Participants are asked to respond to the described experiences by placing marks on horizontal visual analogue scales (VAS), which are anchored as *no, not more than usual* on the left and as *yes, very much more than usual* on the right. It assesses altered states of consciousness produced by drugs such as ketamine, psilocybin or MDMA and the effects of meditation. Their psychometric properties are adequate (Cronbach’s alpha > 0.80) [30, 37].

##### Diary for recording activity

During the intervention and follow-up periods, participants will be asked to record information on the formal practice (number of sessions, total duration, time of day) and on informal practice (duration, time of day) for inclusion as a moderator variable.

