### Statistical analysis

Descriptive data will be visually compared in terms of sociodemographic data, meditation experience and psychological variables across the arms at baseline to ensure balance among groups. They will be summarized using means (SDs) for continuous variables, and frequencies (percentages) for categorical variables. All analyses will follow a pre-specified plan. Outcomes will be compared between groups using the intention-to-treat principle. Missing outcome data (assumed to be missing at random) will be imputed using multiple imputations based on chained equations. The imputation model will include the outcomes at each time point, trial arm, the completion of the training and the extent to which meditation was practised, as well as other characteristics pre-specified for covariate adjustment, generating 20 imputed datasets. The primary analysis will be carried out for NETI total scores at post intervention. Outcomes at each time point will be compared using mixed-effects linear regression models. The main comparisons will be adjusted for baseline scores, gender and age. Means (SDs) will be reported for each trial arm along with the adjusted mean difference between arms, 95% confidence interval (95% CI) and *p*-value for the adjusted mean difference. Results from the complete-case analyses will be also reported, as well as additional sensitivity analyses utilizing complier-average causal effect (CACE)/instrumental variable methods to explore the causal effects of (a) participant engagement with the intervention and (b) regular meditation practice.

An alpha level of 0.05 will be established using a two-tailed test. The probability values relative to the main analysis will be adjusted according to Benjamini-Hochberg’s correction for multiple comparisons, but the secondary analyses will not be corrected.

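### The diary section makes practice recorded after randomisation a moderator; results of that analysis could be spurious, although the primary comparison is unaffected

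*Protocol article*

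**What the plan says.** - **When practice is recorded** (Diary for recording activity): "During the intervention and follow-up periods, participants will be asked to record information on the formal practice", and likewise on informal practice.
- **What it is for** (same section): "duration, time of day) for inclusion as a moderator variable".
- **Practice after treatment** (Interventions): once the 60 days are over, "participants will be able to practise any kind of meditation and at times of their choosing", with the diary still kept.
- **Main analysis** (Statistical analysis): "Outcomes will be compared between groups using the intention-to-treat principle"; "The primary analysis will be carried out for NETI total scores at post intervention"; "The main comparisons will be adjusted for baseline scores, gender and age". Diary practice is not in this list.
- **Other uses of practice** (Statistical analysis): the extent of practice enters the imputation model, and sensitivity analyses are to use "complier-average causal effect (CACE)/instrumental variable methods to explore the causal effects of (a) participant engagement with the intervention and (b) regular meditation practice".
- **Baseline information on meditation** (Sociodemographic data and meditation experience): length of experience, usual minutes per session and "the percentage of their time dedicated to each type of formal meditation", among other items.

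**The concern.** An effect modifier sorts participants by something that would have been the same whichever arm they had drawn. Practice during the 60 days is not of that kind. It may reflect the burden of the technique, how the participant is responding to it, and motivation, which may also raise NETI. Participants know their allocation, so motivation can itself react to it. Within levels of recorded practice the arms are then self-selected groups and no longer randomised ones.

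Practice in follow-up has a further defect. It happens after the primary time point, so it cannot modify the post-intervention effect and may be a consequence of it.

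At stake is a secondary finding such as one technique working better with more practice, or one arm looking superior once practice is held constant. The Statistical analysis section leaves secondary analyses uncorrected for multiplicity, and the Discussion offers the relationship with practice time as something the trial may study. A false result of this kind could therefore be reported as a substantive one.

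**Working it through.** The plan gives no figure for the moderator analysis, so there is none to reproduce. The check sets the sections side by side and then asks how large the distortion could be.

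**1. Can practice depend on arm?** The general instructions in Interventions ask every arm for 30–60 minutes a day. The mirror exercise text gives 30–45 minutes. These two statements need reconciling by the authors. As they stand, recorded minutes can differ by arm through the instructions alone. The documents do not say by how much, and they give no differing range for the other techniques.

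**2. Does practice enter the main model?** No. The stated covariates are baseline score, gender and age.

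**3. Scale.** The Sample size section gives 60 per arm and a post-test difference of 75 − 69 = 6 points for d = 0.5. The implied SD is 6 / 0.5 = 12.

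**4. Formula.** Suppose there is no true arm effect and an unmeasured trait (motivation) correlates r₁ with practice and r₂ with outcome within arm, in SD units. The within-arm slope of outcome on practice is b = r₁ × r₂, none of it causal. If practice differs by Δ SD between arms, a model with arm and practice returns a spurious arm effect of size b × Δ, in favour of the arm that practised less. If r₁ differs by arm, the spurious interaction is r₂ × (r₁ in one arm − r₁ in the other).

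**5. First set of assumptions.** Two arms of 60, 3,000 runs per setting, no true effect, r₁ = r₂ = 0.5, so b = 0.25. The practice model contains arm, baseline, practice and arm × practice; the comparison model contains arm and baseline only. The formula column is signed for the arm that practised more.

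| Practice gap Δ | Formula, −0.25Δ | Simulated arm term | False positives, practice model | False positives, arm + baseline only |
|---|---|---|---|---|
| 0 | 0 | 0.001 | 4.8% | 4.9% |
| 0.3 | −0.075 | −0.074 | 7.4% | 5.3% |
| 0.5 | −0.125 | −0.126 | 12.5% | 5.8% |
| 0.8 | −0.20 | −0.200 | 22.3% | 5.1% |

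In these four settings, where the trait acts alike in both arms, the interaction term is falsely significant in 4.6–5.6% of runs. If the trait drives practice in one arm only, the slope difference is 0.25 − 0 = 0.25 in size, and the interaction is falsely significant in 29.6–31.9% of runs.

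**6. Other assumptions.** Two arms of 60, no true effect, outcome regressed on arm, practice and arm × practice.

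| Scenario | Formula | In points (SD 12) | False positives |
|---|---|---|---|
| Arm term: Δ = 0.3, r₁ = 0.5, r₂ = 0.4 | 0.5 × 0.4 × 0.3 = 0.06 SD | 0.7 | about 6% |
| Arm term: Δ = 0.5, same correlations | 0.5 × 0.4 × 0.5 = 0.10 SD | 1.2 | about 8% |
| Arm term: Δ = 1, r₁ = 0.7, r₂ = 0.5 | 0.7 × 0.5 × 1 = 0.35 SD (0.34 simulated) | about 4 of the planned 6 | 42–44% |
| Interaction: r₁ = 0.6 v 0.4, r₂ = 0.4 | 0.4 × 0.2 = 0.08 | – | about 7% |
| Interaction: r₁ = 0.8 v 0.2, r₂ = 0.6 | 0.6 × 0.6 = 0.36 | – | 53–54% |

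Every correlation and practice gap here is an assumption; none comes from the documents.

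**The case against.** A reader might infer that using practice as a moderator breaks the trial's randomised comparison. The documents do not support that. The main comparison is by intention to treat, on post-intervention NETI, adjusted only for baseline score, gender and age. In the simulations a model of that form kept its error rate near 5% whatever happened to practice.

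A reader might also infer that false findings are likely. That is not shown either. With practice and its confounding alike in all arms there is no bias, and in mild scenarios the error rate is only about 6–8%. The large figures need strong inputs for which the documents give no evidence.

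Further points can be made for the plan. It specifies no arm-by-practice model, so the regression used above is a construction, and a journal article may leave such detail to the full analysis plan. It already assigns the causal effect of practice to CACE/instrumental variable methods, which suggests the authors know that practice is not exogenous. The trial is described as exploratory.

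These points limit the scope of the concern but do not remove it. The role given to the diary data is stated, not left open, and an analysis plan that follows it inherits the error. The CACE analyses are separate sensitivity analyses and do not qualify the diary section. The same variable is thus treated as needing causal methods in one section and as a moderator in another.

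**Conclusion.** The point holds in a limited form. The diary section assigns the role of moderator to a variable measured after randomisation, part of it after the primary outcome. An arm-by-practice analysis done as written would compare self-selected groups. The primary result is not threatened.

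Within the moderator analysis, false-positive rates under a true null range from about 5% (neither practice nor its confounded link with NETI differs by arm) to roughly 20–50% in strong scenarios, with spurious arm effects from zero to about 4 NETI points. This range rests on an assumed unmeasured trait driving both practice and outcome. The differing minutes in the instructions make an arm difference in practice possible, but its size is unknown. That the confounded link differs by arm is plausible and purely assumed. The correction is worth making because it is cheap and concerns secondary analyses that carry no multiplicity correction.

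**What to change.** 1. In Diary for recording activity, replace the moderator role with that of an adherence or exposure measure.
2. Report formal and informal practice by arm, for the intervention and follow-up periods separately.
3. Keep practice in the imputation model and in the CACE/instrumental variable analyses, as already planned. Whether the assumptions of those methods hold is a separate matter.
4. Label any association between practice and outcome as exploratory and non-causal, and relate only intervention-period practice to the post-intervention outcome.
5. Limit moderation tests to variables collected before randomisation. Prior meditation experience (length, minutes per session, share of time by type of practice) and baseline NETI are already available.

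The cost is a short text change before analysis, with no new data and no change to the sample size or the primary model. The downside is that practice time can no longer be claimed as an effect modifier.
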